In emergency care, the option of on-site interpretation is mostly very limited. Migrant and refugee patients in Germany are more likely than Germans to seek paramedic and out-of-hour medical care, however [14, 15]. Especially in out-of-hospital medical emergencies it is crucial for the paramedic staff to understand the current complaints of the patients, their characteristics and duration of acute symptoms as well as pre-existing conditions, allergies, or drug treatments. Communication difficulties can lead to inaccurate initial assessment and misdiagnosis, which may increase the risk of ensuing incorrect clinical decisions and treatment. This can have potentially life-threatening consequences for the patients. It might also cause unnecessary psychological stress to both patients and medical staff.

Some findings have indicated that the quality of care is inferior for patients with limited language proficiency: Language barriers delay transport to hospitals [16], even though in many emergencies, time is a crucial factor for the patient’s outcome. Language barriers may increase the likelihood of (unnecessary) intubation and intensive care during rescue missions with trauma patients [17]. Lee et al. [18] find that language barriers between emergency physicians and adult patients increase the probability of being admitted to hospital – probably partly as a precautionary measure.

Ignorance of the medical history of the patients and/or misinterpretation of symptoms may also lead to incorrect decisions regarding the choice of hospital. Especially in rural areas, paramedics often have to decide whether to take a patient to a small hospital that is close by and provides basic medical care (or choose between different small hospitals that provide different medical specialities such as obstetrics, chest pain units, or stroke units) or to take the road (and the time) to a hospital that offers maximum medical care.

Moreover, the recent Emergency Paramedics Act (Notfallsanitätergesetz, NotSanG) in Germany has given more competence and responsibility to the paramedic staff so that they can autonomously provide therapeutic measures. Understanding the patients’ situations has therefore become even more important for therapeutic decision-making in the field.

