### Clinical trial

In order to evaluate the effect of the developed app, we will conduct a prospective open intervention study. The main purpose of the clinical trial is to assess how the use of the app affects the perceived quality of understanding of non-German-speaking patients from the paramedics’ point of view **(primary outcome)** and how it affects the quality and quantity of information obtained from patients with language barriers **(secondary outcome).** In addition, we will assess whether the tool is perceived as helpful and easy to handle in daily use by the paramedics.

For this purpose, two different patient control groups are recruited and compared with one interventional patient group. Control group 1 consists of German-speaking patients, whereas control group 2 consists of non-German-speaking patients with whom the communication tool is not used. The interventional group consists of non-German-speaking patients with whom paramedics use the tool to communicate with patients. German-speaking control group 1 serves as baseline for on-scene times, intubation rates, and requests for on-scene emergency doctor support. The recruitment period for this group will be at least 12 months because a very large total number of cases is necessary for the selection of matched control groups. By comparing data on control group 2 and on the interventional group, the immediate effect of the tool on communication and information gathering with non-German-speaking patients can be analysed.

As to the primary outcome, we expect that using the tool, paramedics perceive the communication with non-German-speaking patients as easier and more fruitful. Therefore, we will analyse paramedics’ feedback on questionnaires for each emergency drive with foreign-language patients concerning the communication and mutual understanding with patients (see below). Paramedics are asked to report their experience with the tool to assess its acceptance and usability (see above).

Moreover, this study attempts to generate first knowledge about the extent and relevance of language barriers in emergency operations. With regard to the secondary outcome (quality and quantity of information obtained from the patient), we will be able to compare non-German-speaking patients with German-speaking patients and take demographic and medical aspects into account.

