#### Data collection

Within the clinical trial, data from three different sources are collected and analysed. In order to be able to combine these different data sources on a case-by-case basis, the operational number of each emergency case is used as a pseudonym. This is deleted when the data sources have been matched.
Rescue Service Case Protocol (‘DIVI-Protocol’).

It is mandatory to document all relevant medical information of any emergency operation served by paramedics in standardised Rescue Service Case Protocols called “DIVI-protocols” (**D**eutsche **I**nterdisziplinäre **V**ereinigung für **I**ntensiv- und Notfallmedizin e.V., the German Interdisciplinary Association for Intensive and Emergency Medicine). We will obtain and analyse extracted and anonymised information of these rescue service protocols of all rescue missions that occur at the four emergency medical service stations during the data collection period (listed in Table 1). These data will allow us a comprehensive overview of the characteristics of rescue operations with both German- and non-German-speaking patients. This is the first investigation of its kind in Germany. We will also compare the quantity and quality of information between patients in the intervention group and in the control groups and match these data with the questionnaires that paramedics are to fill out on emergencies with non-German-speaking patients and data on the usage of the app (see below).

**Table 1 Tab1:** Data on rescue missions obtained from the DIVI-protocols

**Patient demographics**	• Year of birth • Sex
**Emergency Operation**	• Operation site (apartment, retirement home, work place, sports place, doctor’s practice, birth centre, hospital, public space, road, school, educational facility, mass event, other) • Other involved emergency vehicles (NEF*, RTW etc.) • Time of emergency call (hh-mm) • Time of arrival at emergency scene (hh-mm) • Time of arrival at patient (hh-mm) • Time of departure at emergency scene (hh-mm) • Time of arrival at hospital (hh-mm)
**Emergency Case**	• Paramedic’s description of emergency case: event, patient’s medical history, pre-medication (free text) • (Working) diagnosis (free text) • Necessity of ventilation (laryngeal mask, laryngeal tube, endotracheal intubation)

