**Medical Aspects**	• Initial Glasgow Coma Scale • Initial NACA-Score • Conditions (stroke, seizure, meningitis, syncope, acute coronary syndrome, STEMI, cardiac arrhythmias, pulmonary embolism, heart failure, orthostatic misregulation, pulmonary edema, cardiogenic shock, pacemaker malfunction, asthma attack, COPD, pneumonia, bronchitis, hyperventilation syndrome, aspiration, haemoptysis, acute abdomen, gastrointestinal bleeding, colic pains, enteritis, psychotic disorders, depression, anxiety, intoxication, suicide (attempt), psychosocial crisis, hypoglycaemia, hyperglycaemia, dehydration, uraemia, fever convulsion, pseudocroup, SIDS, near-SIDS, pregnancy, impending birth, (pre)eclampsia, vaginal bleeding, anaphylactic reaction, heat stroke, hypothermia, frostbite, high fever infection, sepsis, septic infection, influenza, hepatitis / hiv, acute lumbago, epistaxis, social problem (without mental disorder), medical treatment complication) • Injuries (skull & brain, face, neck, thorax, abdomen, spine, pelvis, upper extremities, lower extremities, soft tissues)

*Abbreviations*: **NEF***N**otarzt**e**insatz**f**ahrzeug, i.e. non-transporting emergency physician rapid response car, ***RTW***R**ettungs**t**ransport**w**agen, i.e. patient-transporting ambulance, *NACA* National Advisory Committee for Aeronautics, *STEMI* ST-elevation myocardial infarction, *COPD* chronic obstructive pulmonary disease, *SIDS* sudden infant death syndrome

At the emergency medical service stations in Wendhausen, Königslutter, and Helmstedt, the DIVI-protocols are filled in using a laptop device. The responsible district of Helmstedt will provide us a pseudonymised digital dataset. In Braunschweig the staff uses paper DIVI-protocols that will need to be digitalised. Paper protocols will be scanned and processed with the Optical Character Recognition software Form Pro 3.0 (OCR Systeme GmbH Leipzig, Germany), and will subsequently be reviewed to correct misrecognised values.

For the collection and use of DIVI-protocol-based research data, agreements have been reached with the local authorities of the district of Helmstedt and the City of Braunschweig on the basis of existing laws on the execution of rescue services in Lower Saxony.
b)Questionnaire on emergencies with non-German-speaking patients

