#### Data analysis of the clinical trial

Characteristics of intervention and the two control groups are analysed using descriptive statistics regarding their demografics, medical conditions, assessed communication and native languages (where applicable), and aspects of the emergency operation. Differences between patients of the intervention group and the control groups will be tested for statistical significance using Chi-squared or Mann-Whitney *U*-Tests where applicable. In addition, the groups will be compared according to the recruitment centres in which patients were recruited. Relations between medical aspects of the emergency operation or demographic aspects and the assessed mutual understanding will be analysed using correlation analyses. Changes between control group 2 and the intervention group as to the perceived quality of understanding and to the quantity and quality of obtained information of patients will be analysed using paramedics’ feedback on questionnaires and comparing the content of the free text fields in the DIVI-protocols. In order to enable a comparison between non-German-speaking and German-speaking patients, a control group matched by age, sex, medical condition, and emergency situation will be drawn from the very large group of the German-speaking patients. Then, for example, on-scene times, rates of intubations, and requests for on-scene emergency doctor support can be compared.

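### Matching German-speaking controls on the condition the crew recorded may remove or bias part of the language-barrier effect in the exploratory German versus non-German comparison

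*Protocol article*

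**What the plan says.** The section on data analysis of the clinical trial fixes the rule: "a control group matched by age, sex, medical condition, and emergency situation will be drawn from the very large group of the German-speaking patients". It then says that, as examples, "on-scene times, rates of intubations, and requests for on-scene emergency doctor support can be compared". The Clinical trial section gives the German speakers their role: "German-speaking control group 1 serves as baseline for on-scene times, intubation rates, and requests for on-scene emergency doctor support".

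Medical condition is not defined further. Data collection describes three sources. The questionnaire is completed only for patients presumed not to be native German speakers, and the device log exists only where the app is used. That leaves the rescue service case protocol (DIVI) as the one source shared with German speakers. Its candidate fields in Table 1 are a free-text working diagnosis, a list of conditions, injuries by body region, and two severity scores. All are recorded by the crew, and no hospital or adjudicated diagnosis is listed.

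The Background states the risk on which this point turns: "Communication difficulties can lead to inaccurate initial assessment and misdiagnosis, which may increase the risk of ensuing incorrect clinical decisions and treatment". It adds: "Ignorance of the medical history of the patients and/or misinterpretation of symptoms may also lead to incorrect decisions regarding the choice of hospital". The section on integrating the tool into the rescue chain says that the on-scene assessment informs, among other things, whether an emergency doctor is called.

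**The concern.** Matching should balance what was settled before the exposure could act. Here the exposure is the language barrier. By the article's own reasoning, the label the crew writes down may come after that barrier and before the outcomes, which causes two problems.

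- **A blocked path.** If the barrier leads a crew to a different working diagnosis, and that diagnosis triggers a doctor request, comparing patients with the same recorded diagnosis hides that route.
- **Wrong partners.** A foreign-language patient with a mistaken label is paired with a German speaker who truly has that condition. The two differ in true condition, which can shift outcomes such as on-scene time.

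The Discussion expects crews using the app to learn things they otherwise could not. If so, labels may be more accurate in the intervention group than in control group 2, and each would be set against the German baseline with a different bias. At stake is whether a null or altered difference from German speakers reflects care on scene or the matching rule.

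**Working it through.** The article gives no effect size, rate or sample size for the matched comparison, so there is no figure of its own to reproduce. The mechanism can be tested with expected values. **Every rate below is an assumption.**

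**Set-up.** Let s be the true share of severe cases, equal in both language groups (0.2 or 0.3). German speakers are recorded correctly. Among non-German speakers, a non-severe case is recorded as severe with probability f (0 to 0.3), and a severe case as non-severe with probability m (0 to 0.2). The recorded severe share is

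R = s(1 − m) + (1 − s)f.

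Matching on the recorded condition gives the German controls a true severe share of R, while the non-German patients still have s.

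**A. Doctor requests depend only on the recorded condition** (50% if severe, 10% if not). Total effect = 0.4(R − s); matched estimate = 0.

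**B. On-scene time depends on the true condition** (25 v 18 min), plus a real language delay of 3.0 min. Matched estimate = 3.0 − 7(R − s).

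**C. Doctor requests depend on both** (10% base, 20 points for true severity, 20 for recorded severity), plus a direct effect of 5 points. Total effect = 5 + 20(R − s) points; matched estimate = 5 − 20(R − s) points.

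| s | f | m | R − s | A total / matched (points) | B matched (true 3.0 min) | C total / matched (points) |
|---|---|---|---|---|---|---|
| 0.2 | 0 | 0 | 0 | 0 / 0 | 3.00 | 5.0 / 5.0 |
| 0.2 | 0.1 | 0.1 | +0.06 | 2.4 / 0 | 2.58 | 6.2 / 3.8 |
| 0.2 | 0.3 | 0.1 | +0.22 | 8.8 / 0 | 1.46 | 9.4 / 0.6 |
| 0.3 | 0.1 | 0.1 | +0.04 | 1.6 / 0 | 2.72 | 5.8 / 4.2 |
| 0.3 | 0 | 0.2 | −0.06 | −2.4 / 0 | 3.42 | 3.8 / 6.2 |

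Worked line, s = 0.2, f = 0.3, m = 0.1: R = 0.2 × 0.9 + 0.8 × 0.3 = 0.42. In B, non-German patients average 0.2 × 25 + 0.8 × 18 + 3 = 22.40 min and matched German patients 0.42 × 25 + 0.58 × 18 = 20.94 min. The difference is 1.46 min.

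**Difference between groups.** With s = 0.2 and the same 3.0-minute delay in both groups, suppose control group 2 is recorded with f = 0.3, m = 0.1 and app patients with f = 0.1, m = 0.1. The matched estimates are 1.46 and 2.58 min. The gap of 1.12 min comes from the matching alone.

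**The opposite risk.** Leaving condition out is also imperfect. If the true severe share were 0.3 in non-German and 0.2 in German patients, a match ignoring condition would add 7 × (0.3 − 0.2) = 0.7 min of plain case-mix confounding in B.

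**The case against.** The strongest reply has four parts.

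1. **Case mix has to be controlled.** The study-site section describes transit passengers, truck drivers and asylum seekers, who may present differently from local German speakers. Comparing patients managed under the same working diagnosis is also a legitimate direct-effect question; in scenario A, zero is the right answer to it. This stands, and it is why the planned match should stay.
2. **The field is not defined.** A coarse, observable grouping such as injury versus illness would be much less exposed, and such detail may sit in the full protocol. This is partly right. But every candidate field in Table 1 is the crew's own record, and the stated rule carries no restriction to items that need no conversation.
3. **The size is assumed.** This stands. Scenario A's zero follows from how it is built, and the milder cases move 3.0 min only to 2.72 or 3.28 min (the latter at s = 0.2, f = 0, m = 0.2: 3.0 + 7 × 0.04).
4. **Little depends on it.** The abstract calls on-scene times and demand for emergency physicians exploratory, and the app is judged by comparing control group 2 with the intervention group, for which no matching is stated. This stands and limits the weight of the point.

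A reader might go further in three ways that the article does not support:

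- That the article declares the recorded condition distorted. It says only that misassessment can happen.
- That severity matching is compromised through the coma score. Table 1 lists "Initial Glasgow Coma Scale" as a data item, but it is not a named matching variable.
- That the secondary outcome is compromised, since the article also plans to "compare non-German-speaking patients with German-speaking patients and take demographic and medical aspects into account". It does not say that this adjustment uses the recorded condition or the matched set.

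Nor is the recorded case mix hidden: descriptive reporting of medical conditions by group is already planned.

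**Conclusion.** The point holds as a cheap improvement to an exploratory analysis. As written, the rule may condition on a consequence of the language barrier, and so may remove or bias the part of the barrier's effect that runs through misassessment. The bias can go either way: in the calculations, over-recording of severity shrinks a 3.0-minute delay to as little as 1.46 min, and under-recording inflates it to as much as 3.42 min. These figures illustrate the mechanism and do not predict the trial's result. In the calculations the bias vanishes if the condition is recorded equally accurately in both language groups, which the Background gives reason to doubt but does not disprove.

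The unmatched comparison of control group 2 with the intervention group, including the primary outcome, is untouched. Any difference in bias between those groups matters only where each is set against matched German speakers.

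**What to change.** Keep the planned match, and run and report beside it a second match on Table 1 fields that do not depend on conversation: age (from year of birth), sex, operation site, time of the emergency call, and presence and body region of injury.

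State in the analysis section that the match without condition targets the total effect of the language barrier, and that the match with condition targets a direct effect given the recorded condition. Add that the latter is clean only if the label is equally accurate in both language groups. Draw a conclusion about the barrier only in the light of both results: agreement is reassuring, and a clear divergence should be reported as sensitivity to the matching rule.

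The cost is a few sentences and one more analysis run on fields already extracted. The downside is coarser control of case mix in the second match, so it should stand beside the planned match and not replace it.

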#### Inclusion criteria for patients

Patients who meet the following criteria are eligible to participate in the study:
Control group 1: German-speaking patients of all ages who do not use the app.Control group 2: Non-German-speaking patients of all ages who do not use the app (i.e. within the first period of recruitment and because of drop-out in the second recruitment stage)Interventional group: Non-German-speaking patients of all ages who speak one of the available languages (cp. Table 2) and who are responsive to use the app.

**Table 2 Tab2:** Supported languages

• Arabic: possible dialects are Syrian Arabic, Egyptian Arabic, Moroccan Arabic (spelling Modern Standard Arabic) • Bosnian • Croatian • Czech • Dari • English • French	• Italian • Kurdish: possible dialects are Sorani and Kurmanji • Lithuanian • Pashto • Persian • Polish • Russian • Serbian • Turkish

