#### Drop-out criteria for patients from the interventional group

When the intervention takes place, paramedics can refuse to use the app at any time. They are not to use the app when it presumably places the patient or themselves at risk (e.g. rescue operation on a busy and unblocked motorway). Furthermore, the app is not to be used in emergencies with immediate action implications (e.g. cardiopulmonary resuscitation or transport to the hospital necessary without any delay) or if the patient has a severe limitation of consciousness. If patients do not speak languages provided in the app (cp. Table 2), they are excluded from the interventional group but serve as control patients in group 2. Patients who meet the eligibility criteria but with whom paramedics do not use the intervention will be analysed separately.

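### The matching set for the German-speaking comparison omits app eligibility, recorded severity, station and study phase, so app patients set against control group 1 can differ for reasons other than language or the app

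*Protocol article*

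**What the plan says.** The protocol article gives control group 1 a definite role (Clinical trial): "German-speaking control group 1 serves as baseline for on-scene times, intubation rates, and requests for on-scene emergency doctor support". Its only entry condition (Inclusion criteria for patients) is "German-speaking patients of all ages who do not use the app".

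The app group is narrower. Patients must speak a supported language and be responsive. Under Drop-out criteria for patients from the interventional group, the app is not used in resuscitation, when transport cannot wait, in scenes that seem to put patient or staff at risk, "or if the patient has a severe limitation of consciousness". Paramedics may also decline to use it.

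The section Data analysis of the clinical trial then says that "a control group matched by age, sex, medical condition, and emergency situation will be drawn" from the German-speaking patients, after which "on-scene times, rates of intubations, and requests for on-scene emergency doctor support can be compared". The same section plans tests between the intervention group and the control groups, in the plural, and a comparison by recruitment centre. The abstract says that both control groups are recruited from the first study phase and the intervention group only in the second.

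**The concern.** The app's exclusions are defined by urgency and consciousness. Those features also drive intubation, calls for a physician and time on scene. If app patients are compared with a German-speaking pool that has no such limits, the two groups can differ on these outcomes even if neither language nor the app has any effect.

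Station and phase add to this. Study site and study setting describes one city station and three rural ones, often far from a hospital. Foreign transit patients are concentrated at Wendhausen and Helmstedt, and refugees at Braunschweig. Language group and station are therefore likely to be associated, and so may be station and on-scene time. App patients come only from the second phase, while nothing requires their matches to come from it.

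At stake is a reader crediting the app, or the removal of a language barrier, with fewer physician calls or intubations that reflect who was allowed into the app group.

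**Working it through.** The article states no sample size, power or effect for this comparison, so there is no figure of its own to reproduce. The check sets the passages side by side and then gives an illustration of size.

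**1. Matching set against recorded variables.** Named for matching: age, sex, medical condition, emergency situation. Table 1 lists initial GCS, initial NACA score and conditions as separate items, so medical condition does not naturally include the first two. A conscious stroke patient could be matched to an unconscious one. Emergency situation is not defined. Station and phase are not named.

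**2. Which comparison is affected.** The matching sentence opens "In order to enable a comparison between non-German-speaking and German-speaking patients" and does not single out the app group. However, the Clinical trial section compares both control groups with the intervention group, and the analysis section tests the intervention group against the control groups. A comparison of app patients with control group 1 is therefore within the plan.

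**3. Illustration with no app effect and no matching.** Inputs:
- 18% of missions have a physician on site (Background, a national figure).
- On-scene time is 16.9 min with and 22.3 min without a physician (Background, national averages, taken as printed and read as on-scene time).
- There are 50 to 75 patients per group (Sample size estimation).
- Two-sided alpha of 0.05 is assumed.
- f, the share of physician-attended missions in which the app cannot be used, is assumed; the article gives no value. For simplicity, no other missions are removed.

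Attendance in the app group: q = 0.18(1 − f) / [0.18(1 − f) + 0.82].

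False-positive chance: Φ[(0.18 − q − 1.96·SE0) / SE1], with SE0 the pooled and SE1 the unpooled standard error. For f = 0.5 and 75 per group: q = 0.090/0.910 = 0.099, difference 0.081, SE0 = 0.0566, SE1 = 0.0562, so Φ(−0.53) = 0.30.

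Mean on-scene time: 16.9q + 22.3(1 − q). In the unrestricted pool it is 0.18 × 16.9 + 0.82 × 22.3 = 21.33 min.

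| f (assumed) | Attendance, app group v pool | False positives, 50 per group | False positives, 75 per group | Shift in mean on-scene time |
|---|---|---|---|---|
| 0.25 | 14.1% v 18% | 8% | 9% | +0.21 min |
| 0.50 | 9.9% v 18% | 21% | 30% | +0.44 min |
| 0.75 | 5.2% v 18% | 52% | 69% | +0.69 min |

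If the same exclusions were applied to the German-speaking pool, this shift would be zero under no app effect.

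**4. Station.** The pool is 1600 + 3500 + 6200 + 3500 = 14,800 missions a year. The shares are Wendhausen 10.8%, Königslutter 23.6%, Helmstedt 41.9% and Braunschweig 23.6%. (Sample size estimation calls this pool control group 2, but it describes the German-speaking patients.) No outcome figures by station or phase are given, so these two biases cannot be sized.

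**The case against.** The strongest reply is that the matched comparison concerns language, not the app. The app's effect is assigned to control group 2 against the intervention group. If all non-German-speaking patients were compared with German speakers, resuscitation and low-consciousness cases would appear on both sides. That is right, and on that reading the eligibility problem largely falls away. The station and phase gaps would remain. The article does not say which patients make up the non-German-speaking side, and it sets aside for separate analysis eligible patients with whom the app was not used.

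A reader might infer that the plan ignores station and severity altogether. The documents do not support this. A comparison by centre is planned, the abstract says severity is considered through clinical parameters, and condition and emergency situation may capture part of the exclusions. What is missing is these factors in the stated matching set; a comparison by centre, as described, does not adjust the matched contrast.

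A reader might also infer that the groups differ by construction, or that intubation in the app group is near zero by rule. No passage states an intubation rule or rate, and how much difference survives the matching is unknown. Phase bias is possible rather than shown, because control group 1 is recruited from the first phase for at least 12 months and concurrent controls may exist.

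It is tempting to add recording differences, since "In Braunschweig the staff uses paper DIVI-protocols that will need to be digitalised". But the scans are reviewed for misread values, and the outcomes named for the matched comparison are not the free-text fields.

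Finally, on-scene time and physician demand are called exploratory in the abstract, and all three outcomes appear in the analysis section only as examples. This limits the consequence, but the stated matching set still needs correcting.

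**Conclusion.** The concern holds in a limited form. The stated matching set omits station, phase, GCS and NACA score, and control group 1 is not restricted to patients with whom the app could have been used. A comparison of app patients with that baseline can therefore be biased on outcomes closely tied to the app's exclusions.

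The size is uncertain. The range of 9% to 69% false positives at 75 per group rests on an assumed f of 0.25 to 0.75, on a national attendance rate used in place of requests at these stations, and on no matching at all. It is an upper-end illustration, since matching would remove an unknown part. The primary outcome and the main contrast for the app, control group 2 against intervention, are not touched by this point. The change is worth making because it is cheap and the variables are already collected.

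**What to change.** In Data analysis of the clinical trial, for the comparison of app patients with control group 1:

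1. Restrict the German-speaking pool to patients with whom the app could have been used, as far as recorded GCS, NACA score and conditions show this.
2. Match on station and study phase, add initial GCS and NACA score to the matching set, and define emergency situation.
3. Analyse the matched sets with a method that keeps the matching.
4. Report app-treated and untreated non-German-speaking patients separately, and say which of them each comparison with German speakers uses.

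No rule on when the app may be used needs to change. The cost is analysis wording, more analysis work and somewhat fewer usable controls, which a pool of about 14,800 missions a year can bear. The restriction will be approximate: scene risk, paramedic refusal and urgency of transport are not fields in Table 1, and this should be stated as a limitation.
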